##### *¡Míranos!* PA/gross motor program

Head Start children will participate in daily PA (30-min structured and 60-min non-structured play) during outdoor/indoor play, learning center time, and transitions. Teachers will use *¡Míranos!* Activity Cards (at least one card/day) and equipment supplied by the study to meet the PA goals (see Additional file 1 for samples of Activity Cards). The Activity Cards are written lesson plans to increase MVPA and teach age-appropriate gross motor skills in structured and unstructured group formats for outdoor and indoor settings. The Activity Cards were designed by physical education specialists according to principles of motor development and can also be used during transitions and learning centers. Portions of the Activity Cards are written based on the storylines of 21 children’s books with nutrition and PA themes that can be readily integrated into daily routine activities (e.g., story time, transition). We also created active learning activities (e.g., learning ladders) that combine literacy and numeracy skills with physical activities, which can be used by the learning centers to increase opportunities for PA. Teachers will also use age-appropriate movement music CDs and dance videos that can be used for brain break activities after 15-min sedentary time and provide PA alternatives for indoors and bad weather days. The teachers will identify and include the structured and non-structured activities into their daily lesson plans. We will develop a training DVD to detail lesson implementation and demonstrate gross motor activities to help teachers develop confidence and overcome challenges in leading the activities and to reinforce key concepts from the staff training.

##### Supplemental health education activities

The Sesame Workshop bilingual Healthy Habits for Life (HHL) resource kit is the primary source for health education. The HHL uses Sesame Street cartoon characters to promote PA and healthy eating in children aged 3–5. There are 9 modules with short, age-appropriate learning activities, hands-on games, and interactive DVD activities (The Get Healthy Now Show) that can be integrated into daily center routines. Each module has a “Did You Know” fact to promote a key health message to children and parents. At least one storybook will be introduced during story time that is related to the weekly topic of the HHL. Head Start teachers will incorporate HHL activities into their daily lesson plans with a goal of using all activities in each module at least once a week. Health contests will be conducted to increase PA and intake of water, fruit, vegetables, and reduce TV watching and sugar-added drinks in accordance with HHL topics. “Did You Know” facts will be displayed with signboards at center entrance and classrooms to promote evidence-based health messages to children and parents.

The Head Start center directors and teachers will integrate PA and nutrition education activities into daily lesson and routines following the *¡Míranos!* master intervention schedule during the biweekly lesson planning required by Head Start standards of practice. The *¡Míranos!* master intervention schedule shows the coordination and outlines the weekly activities for each component of the CBI. The teachers will submit their lesson plans to the center director for review and feedback. Table 4 shows the expectations and goals for Head Start teachers to deliver the center-based activities. To facilitate the integration of the intervention activities by Head Start teachers, we created a *¡Míranos!* eBook that provides weekly intervention schedules, electronic copies of intervention activities, access to online movement music and videos, and online audio/video versions of the children’s storybooks. Each teacher and center director can access the content of the eBook on an Android tablet. Each intervention classroom is equipped with a Smart TV monitor that can be linked to the eBook to display the eBook content (e.g., HHL poems, HHL video, electronic storybooks) and to show GoNoodle videos and other music videos to the children in the classroom for bad weather days and for transition activities.

#### ¡Míranos! Staff wellness program

A staff wellness program, which consists of a staff wellness manual and challenges, was developed to align with the *¡Míranos!* curriculum with the goal of encouraging staff to improve their own health and become healthy role models for the children at the center. The staff wellness manual, created based on information provided by the US Dietary Guidelines for Americans 2015 and the Centers for Disease Control and Prevention, utilizes Knowles’ Principles of Andragogy to establish topic relevance and social cognitive theory to enhance self-efficacy through goal-setting. The manual contains three main sections: 1) physical activity and hydration; 2) fruits and vegetables; and 3) overall wellbeing. Each section provides benefits for each health behavior, evidenced-based recommendations, examples and tips, suggested exercises or recipes, and goal-setting worksheets. Detailed instructions for use are included along with a weekly calendar that assigns staff wellness manual sections and staff wellness challenges to the *¡Míranos!* content at each site. Center-wide staff challenges, initiated by the center director, coincide with the children’s health contests. Each center director will post flyers 1 week prior and during the staff challenge to encourage participation. Posters to track staff progress will be posted in a staff-only area and center directors will report the number of staff who participated in the challenge and who achieved their goal to receive cash incentives for their center. Participation in the staff wellness program is voluntary and coordinated by the center directors.

#### Home-based intervention

The home-based intervention (HBI) arm of the *¡Míranos!* study is designed to engage parents/guardians of Head Start children and to educate them on child obesity prevention. Centers assigned to the HBI will provide parent education through several components, including peer-led obesity education, newsletters, family health challenges, and home visits with Head Start staff. The HBI consists of eight peer-led parent education sessions with take-home activities, eight family health challenges, sixteen parent newsletters, summer resource packet, and three home visits.

##### Peer-led obesity education

Head Start requires parents/guardians to physically sign their child in and out of the center. Seizing on this opportunity to engage parents, trained Head Start parents will deliver eight monthly peer-led education sessions using wall posters, live demonstrations, and instant feedback during child pick-up time. A wall poster session can be completed in 15–20 min. During the education sessions, six posters will be used to highlight parental beliefs and practices and to teach current guidelines and recommendations for child PA and nutrition. Use of posters in education sessions also allows peer educators to promote evidence-based strategies related to positive child feeding, increasing PA and sleep duration, reducing screen time at home, and limiting sugary drinks and promoting water. Session topics and activities are displayed in Table 6. All wall posters will be bilingual.

**Table 6 Tab6:** Parent education poster session topics

Session #	Topic
1	Overview of *¡Míranos!*
2	Physical Activity Benefits and Recommendations
3	Limiting Screen Time at Home
4	Balanced Diet and Expert Recommendations
5	Keeping Healthy Foods in the Home
6	Promoting a Balanced Diet and Healthy Eating Habits
7	Promoting Physical Activity Indoors and Outdoors
8	Sleep, Bedtime Routine, and Expert Recommendations

##### Peer educator training

The Head Start Center Director/Operator at each center will identify and recruit four to six parents from their center to serve as peer educators and deliver the sessions. Qualifications include speaking English and Spanish and a history of volunteering at a center. Peer educators will receive a small stipend (up to $240) to participate in multiple trainings and deliver the sessions, for a total of 32 h of work across 8 months.

##### Take-home bag

During peer-led education sessions, parents will be asked to complete a scavenger hunt, a sheet of paper with six questions that pertain to the session topic (e.g., True or False? Experts recommend that preschoolers get at least 2 h a day of physical activity). Answers to the scavenger hunt questions are found by visiting the posters and interacting with peer educators. Parents who complete the scavenger hunt will receive a take-home bag that includes a health-themed storybook, a bilingual, family activities newsletter, and a developmentally-appropriate interactive game.

##### Family newsletter

As part of the HBI, 16 biweekly, bilingual *¡Míranos!* Health Newsletters will be sent home in take-home bags at the end of each education session (*n* = 8 newsletters) and in the child’s daily home folder (*n* = 8 newsletters). These newsletters, designed for 5th-grade reading comprehension, will provide information and tips for parents/guardians to help modify their family’s health behaviors related to physical activity, diet, screen time, and sleep so that they can support and role-model to their child. Additionally, each newsletter provided in the take-home bag will provide a culturally appropriate healthy snack or meal recipe that parents can easily make at home, as well as a low-cost or free community resource (e.g., a city park or event) that parents can attend with their children to help promote a healthier lifestyle.

##### Family health challenge

Immediately following each peer-led education session, parents will receive a “Family Health Challenge” form in their child’s take-home folder that involves the whole family on a targeted health behavior (e.g., drinking water, limiting screen time, and increasing physical activity) that relates to the topic of the education session. Parents will be able to choose from one of three challenges for their family to complete over the course of 7 days. Parents will mark on the form whether or not they completed the challenge. Children whose parents have returned a completed health challenge form will have their names publically displayed in a poster in the classroom.

##### Home visits

Per Head Start standards, Head Start Family Service Workers who have training in social work conduct two home visits per year at a minimum (~ 30 min/visit), and additional visits if needed. During the visits, the Family Service Workers will identify needs and issues, devise an improvement plan, if needed, and provide monitoring and support to parents. We will integrate a protocol into three home visits to develop skills and strategies for parents to promote PA, nutrition, screen time, and sleep at home. Each home visit will have two different health topics that Family Service Workers will introduce to the parent. Home Visit 1 will focus on increasing physical activity and limiting screen time, Home Visit 2 on increasing fruit and vegetable intake and limiting sugary drinks, and Home Visit 3 on healthy eating practices and sleep. As part (~ 15 min) of each home visit, the Family Service Worker will review the two health topics with the parent by providing an informational handout. The parent will then choose one of the health topics to set a family goal and develop a *¡Míranos!* Action Plan (a log for parents to document their participation and progress per the Head Start requirement). The Family Service Worker will guide the parents to establish family rules and develop strategies from a menu of evidence-based strategies to achieve their goal and make the home environment more conducive for healthy behaviors. For example, to implement the rule of sleeping ≥10.5 h/d, parents can remove TVs from children’s bedrooms and establish bedtime routines. The Family Service Worker will record the parents’ chosen rules and strategies in the *¡Míranos!* Action Plan and follow-up with parents after 1 month to track progress. At Home Visits 1 and 3, the Family Service Worker will ask parents to complete the Home Environment Questionnaire to identify the availability and accessibility of healthy and unhealthy foods in the home, electronics and play equipment in the home, and child sleep duration and bedtime routines. This will allow research staff to determine whether home visits impacted the home environment*.*

#### Staff development and training

We will provide development training 1) to increase Head Start staff health literacy (e.g., knowledge in obesity, nutrition, and PA), and instruction and management skills (e.g., role-modeling, PA skill demonstration, and leading activities, positive reinforcement), and 2) to implement ¡*Míranos!* intervention activities. All Head Start staff, including teachers, teaching assistants, Family Service Workers, center directors, food service workers, and custodians, will complete a paid training of up to 20 h depending on the roles of the staff in the study. The training includes online didactic education modules on physical activity and nutrition (8 h, required for all staff) and two half-day in-person training sessions (4–12 h, required depending on roles in the study). The in-person training is designed to familiarize the staff with the ¡*Míranos!* intervention protocol and the physical activity and nutrition policy modifications. Training topics include the study overview and protocol (1.5 h); center policy modifications (1 h); intervention program components (1.5–2.5 h); intervention coordination (30 min); physical activity and gross motor skill instruction (50 min); demonstration of *¡Míranos!* gross motor and physical activities for outdoor and indoor settings, transition and active learning activities, and use of equipment (2 h); health/nutrition education and instruction (50 min); demonstration of *¡Míranos!* health education activities, equipment, and supplies (40 min); and administrative issues (1 h).

Family Service Workers will receive separate training to implement the HBI. Each month, the peer educators will attend a training (1.5*)* with the Head Start Education Specialist (ES) or Education Center Coordinator (ECC) assigned to their center to prepare for parent education sessions. During trainings, peer educators will review information about the topic for the session (i.e., Physical Activity Recommendations and Benefits, Balanced Diet Recommendations, Keeping Healthy Foods in the Home, etc.) by watching a short (10–15 min) video, developed by research staff, that leads peer educators through the information displayed on each of the 6 posters for that session. Peer educators will also receive poster scripts, documents that contain key information for each of the posters that peer educators should relay to parents attending the education sessions. The poster scripts reflect the information presented in the training videos and are supplements that the peer educators will use during education sessions. Peer educators will actively practice the session content by role-playing during each training. Peer educators will pair up and take turns playing the role of center parent while the other practices poster content. At the end of each training, ES/ECC will prompt peer educators to discuss anticipated or experienced challenges during education sessions and problem-solve to address any identified challenges for the next education session.

Booster trainings (5 h) will be conducted to provide additional training based on needs during the year. Additional training will be provided at a later time to those who did not complete the initial training. All peer educators will receive a certificate upon completing the training. We will also develop the training of the Family Service Workers in implementing the home visits, including conducting home audits, developing the *¡Míranos!* Action Plan, and counseling/problem solving. We will make a DVD of training modules for staff, Family Service Workers, and peer educators that can be used later to train new staff.

#### Comparison condition

The study Head Start organizations have adopted “I Am Moving, I Am Learning” (IMIL) as its required PA and nutrition curriculum since FY 2012. IMIL is an obesity prevention program developed for and endorsed by Head Start for increasing the time in MVPA and structured PA and encouraging children to take healthy food choices by educating Head Start staff and parents. Head Start directors and staff can design their own program using activities and materials (games and gross motor activities, one set of play equipment, nutrition activities, and parent newsletters) from an IMIL kit after a brief training by an IMIL facilitator. The control centers will continue using IMIL. Although a classic “no treatment” control is common in RCTs, our study participants and partners are more receptive to a control condition that offers some attention and benefits. All comparison children will get some education on PA and nutrition via IMIL; in addition, we will deliver a literacy education program to children in comparison centers to increase buy-in and retention. The literacy education program, called Book Bites sponsored by a local grocery chain, will include 30-min sessions that incorporate early childhood literacy and nutritional concepts through interactive book reading activities.

### Trial flow

Figure 2 provides an overview of the trial flow for the study.

**Fig. 2 Fig2:**
[figure not shown]
Study Participant Flow

### Study measures

Data will be collected to assess the primary and secondary study outcomes as well as mediation/moderation measures to evaluate the impacts of the intervention. Table 7 shows the measurements and assessment timelines for the study. We have selected the measures that have established validity and reliability in the study population. All measures for the parents are offered in English and Spanish. To increase parental participation and compliance with assessment protocol, we will provide incentives (up to $30) that are linked to returning daily food/screen time/sleep logs ($3/d) and parent surveys ($9 and raffles for tricycle) at each assessment time. Prior to each data collection, we will provide training on data collection protocols, including privacy protections, to all assessment staff..

**Table 7 Tab7:** Study measures and assessment timelines

Primary outcomes	Baseline	Posttest	Follow-up
Height, weight, Body Mass Index (BMI; kg/m^2^); BMI z-score [59]	C	C	C
Secondary outcomes			
7-day accelerometry for PA, sedentary time and sleep [60]	C	C	C
The Test of Gross Motor Skills	C	C	C
Aggregated plate waste test^,^ (241)	C	C	C
National Health and Nutrition Examination Survey (NHANES) Dietary Screener			
7-day logs for child screening and sleep time (min/d) [61]	P	P	P
Computer-assisted pictorial test for food preferences [62]	C	C	C
Mediator/moderator measures			
The Home Self-administered Tool for Environmental Assessment of Activity and Diet [63]			
The Parenting Strategies for Eating and Activity Scale [56]	P	P	P
Parent health knowledge test [43]	P	P	P
Parental confidence/self-efficacy scale [64]	P	P	P
Food Behavior Checklist [65]	P	P	P
Acculturation scale [66–68]	P		
Parent weight and physical activity [69]	P	P	P
Family socio-demographics/health history	P		

Data source: *C* child, *P* parent, *S* staff

The primary outcome of the study is child’s BMI calculated as weight in kilograms divided by height in meters squared. Child’s height and weight will be measured twice at the beginning of the school day with no shoes and light clothes, using a stadiometer and digital weight scale. Discrepancy between the two measures must be ≤0.5 cm and ≤ 0.25 kg. We will measure every fifth child by two staff to assure the accuracy and reliability of the weight and height measures.

BMI, BMI-percentile, and zBMI for age and gender will be calculated using the average of the two measures-based child growth charts [59]. We chose change in BMI as the primary endpoint because BMI is within-child referenced [70] and more suitable for assessing change in adiposity in intervention studies of same-age children during the adiposity rebound period [71], compared to zBMI and BMI-percentile. BMI also correlates better with directly measured adiposity in young children [71, 72]. We will analyze zBMI as an outcome measure as well [73]. The selection of the measures for the secondary outcomes and mediation/moderation effects are intended to examine the pathways of influences of policy and behavior changes in the primary outcome depicted in the conceptual model of ¡*Míranos!* intervention. Previous research has shown that these measures play key roles in influencing the levels of obesity in children who participate in lifestyle intervention studies.

### Process evaluation

*The design of* process evaluation is informed by the NIH Behavior Change Consortium Treatment Fidelity Workgroup’s best practice recommendations [74] and recent multi-component RCTs [75]. Because *¡Míranos!* has multiple components with multiple activities, we will use multiple indicators to evaluate the fidelity and completeness of the implementation of all components and determine contribution of each component by linking it to the primary and secondary outcomes. We will collect both quantitative and qualitative data to assess cross-site treatment consistence and non-treatment-related effects [74] and document protocol changes [75]. The evaluation will target three aspects of intervention implementation.

First, the intervention dose delivered (i.e., the extent to which the intervention is delivered as planned to Head Start staff, children and parents) will be measured by: 1) pre- and post-study center environmental assessment by the Environment and Policy Assessment and Observations (EPAO) and auditing of meal menus; 2) completion of delivery schedule of staff and peer leader training, parent education sessions and home visits; 3) evaluation of staff and peer leader training; 4) monthly auditing of weekly lesson plans; and 5) monthly checklist of use of *Míranos!* Activity Cards, children’s story books, and HHL learning activities.

Second, the intervention dose received (i.e., the extent to which Head Start children and parents understand and learn the knowledge and skills delivered in the intervention by Head Start staff) will be assessed by: 1) attendance records of staff and peer leader training and parent education sessions; 2) certification test of staff and peer leader training; 3) monthly staff evaluation (rating scale) of children’s learning of HHL content, gross motor skills and eating behaviors; 4) post-study parent intercept interviews; and 5) post-study focus groups on program delivery process with staff (*n* = 24) and parents (*n* = 32).

Third, participants’ responses to the intervention (i.e., the extent to which Head Start staff, children and parents use and apply the knowledge and skills learned in the intervention in daily life) will be evaluated by: 1) quarterly observation of staff behavior (rating scale) during outdoor play and lunch by research staff; 2) quarterly assessment on children’s PA by the System for Observing Fitness Instruction Time for Preschoolers [76] and diet by group plate waste test [77] in three randomly selected centers; 3) pre- and post-study home environmental changes by HomeSTEAD [63] and the use of *Míranos!* Action Plan by the parents; 4) in-depth interviews with staff (*n* = 48) for program feedback; and 5) post-study staff and parent evaluation (rating scale) of satisfaction with intervention components/activities.

#### Data analysis plan

For Hypothesis 1, we will first calculate the change in BMI at T1 from T0 and at T2 from T0 for each child. We will then compare the difference in change scores among the three intervention groups using ANOVA test or Kruskal-Wallis test at each time point separately. Multiple comparisons defined by various linear combinations of groups (i.e., CBI-control; C&HBI-control) will be performed to exam the difference in change scores with Bonferroni adjustment. To utilize all three measures from each child, generalized linear mixed effects models (GLMMs) will be used to examine the group differences at different time points with BMI as the response variable, and time (3 levels: T0, T1 and T2) and group (3 levels) and their interaction as the explanatory variables. Two random effects will be included in a GLMM: one to account for the correlation among children nested within the same center, and one to account for the three repeated measures of each outcome within the same child. Center size and cohort, as fixed effects, will be included in the model as well. We will also include baseline BMI, child gender and race/ethnicity, and other covariates (e.g., parent characteristics and health behaviors) in the model as needed. Model fit will be assessed by residual diagnostics [81] to guide the best fit model. For Hypothesis 2, we will use the same statistical procedure for testing Hypothesis 1 to analyze the secondary outcome measures (i.e., MVPA, sedentary behavior, TV watching, sleep, and dietary measures), with baseline BMI as a covariate as well to check for differential effect of intervention associated with children’s level of adiposity. When there are missing data, we will compare the dropouts and completers on demographics and various outcome measures using available data. If data are missing at random (MAR) [82], standard computational algorithms such as EM implemented in statistical software allow the use of all the data available to generate appropriate parameter estimates. If the MAR assumption is in doubt, we will conduct sensitive analysis to impute missing data using the multiple imputation with chained equations approach [83]. Specifically, we will impute missing values by adjusting for time of measurement and demographics to create 10 imputed datasets. We will then combine the effect sizes using the Rubin’s rules [84]. Stata/SE (version 15, College Station, Texas) or SAS (version 9.3, Cary, North Carolina) will be used for conducting all analyses proposed.

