## Methods and design

### Design and study aims

The study will use a cluster randomized controlled design to test the efficacy of the ¡*Míranos*! intervention in preventing excessive weight gain and promoting the development of healthy habits in young children enrolled in Head Start. The primary end point for the study is a change in BMI at the posttest (7 mo from baseline). Using a three-arm design, 12 Head Start centers will be randomly assigned to one of three conditions in equal number: 1) a combined center- and home-based intervention, 2) center-based intervention only, or 3) comparison. The interventions will be delivered by trained Head Staff staff during the academic year. A total of 444 3-year-old children (*n* = 37 per center) will be enrolled in the study in two cohorts at baseline and followed prospectively 1 year post intervention. The first cohort will be recruited between May 2018 and September 2018. The second cohort will be recruited between May 2019 and September 2019. Outcome assessment will be conducted at baseline (T0), immediate post-intervention (T1), and at the one-year post-intervention follow-up (T2; 21 mo from baseline). The assessment at each time point will take up to 4 days to complete at a center, depending on the size of the center enrollment. We will divide the 12 centers into four groups to assure the manageability of data collection and the intervention delivery. Each group includes a center from each condition to control the extraneous conditions (e.g., weather conditions, organizational events) and secular trends. The intervention will commence in the week following the completion of the assessment.

Specific aims and hypotheses of the study are to:

Aim 1: Test the efficacy of the *¡Míranos!* intervention on healthy weight growth measured by BMI change (primary outcome) in normal weight, overweight and obese children. Hypothesis 1: Children in the combined center- and home-based or center-based intervention conditions will have a significantly smaller increase in BMI (kg/m^2^) compared to children in the comparison condition at T1 and T2.

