### Study setting, recruitment, and randomization

Two Head Start administrators in San Antonio, Bexar County, Texas have joined the study as collaborators and agreed to randomize their centers as the study sites. Both organizations have previously worked with the study team in developing and piloting the intervention program. The two organizations represented by these administrators oversee 49 Head Start centers with a total enrollment over 2000 children. According to the published eligibility criteria of the Administration for Children and Families of the U.S. Department of Health & Human Services, “children from birth to age five who are from families with incomes below the poverty guidelines are eligible for Head Start and Early Head Start services.” Children from homeless and foster families and families receiving other forms of public assistance are also eligible. The study eligibility criteria for the centers and children are displayed in Table 1. Children will not be excluded from the study if they do not speak English or have limited English proficiency. After discussing the eligibility issues with the two Head Start organizations, the research team determined that three centers from organization A and nine centers from organization B that meet the center inclusion eligibility criteria will become the study sites. Using statistical software R (version 3.3.2), the centers are randomly assigned to one of the three treatment conditions stratified by the organizations and the center enrollment size so that the centers from both organizations are equally represented in the study.

**Table 1 Tab1:** Study eligibility criteria

Center eligibility	1. A full-day center (offering ≥7 h of care/day)
	2. At least one classroom enrolling children aged 3
	3. Agreement to modify center physical activity and nutrition policies
	4. Agree not to participate in other health-related studies.
Child eligibility	1. Enrollment in a study center
	2. Age 3 years at baseline
	3. One child per family
	4. Parental consent

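### With T0 BMI among the responses and group-by-time the only interaction named, center size and cohort leave the group differences in BMI change essentially unadjusted

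*Protocol article*

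**What the plan says.** All references are to the protocol article.

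- **Design and study aims.** "The primary end point for the study is a change in BMI at the posttest (7 mo from baseline"). Hypothesis 1 says that children in either intervention arm "will have a significantly smaller increase in BMI (kg/m^2^) compared to children in the comparison condition at T1 and T2". Both concern change.
- **Data analysis plan, mixed model.** The model "will be used to examine the group differences at different time points with BMI as the response variable". Its explanatory variables are "time (3 levels: T0, T1 and T2) and group (3 levels) and their interaction as the explanatory variables". There is a random effect for child and "one to account for the correlation among children nested within the same center". Then: "Center size and cohort, as fixed effects, will be included in the model as well". Baseline BMI, gender, race/ethnicity and parent variables may be added as needed.
- **Data analysis plan, first step.** Change scores are compared by ANOVA or Kruskal-Wallis with Bonferroni adjustment. No covariates are named there.
- **Study setting, recruitment, and randomization.** Centers are randomized "stratified by the organizations and the center enrollment size".

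Group-by-time is therefore the only interaction in the text, and the mixed model is the only Hypothesis 1 analysis that is said to include covariates.

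**The concern.** Center size and cohort do not vary over a child's three visits. As main effects in a model where T0 is an outcome, they explain differences between children in BMI level. They say nothing about how BMI changes, which is the subject of the primary endpoint.

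The mixed model is the one place where the plan accounts for a stratification factor and for recruitment year. A reader would take its results as adjusted for both, yet for change they would not be. Children are recruited in 2018 and 2019, and the article does not fix the cohort split within a center. If growth over seven months differs between cohorts, a chance difference in cohort mix between arms stays in the arm contrast. If center size is related to change, its variation stays in the error term although randomization was stratified on it.

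**Working it through.** **The plan's own figure.** The sample size is not affected, but it reproduces. The article gives 4 centers per arm, 29 children per center, a difference of 0.53, SD 1.147, ICC 0.003 and two-sided 5%.
- Design effect: 1 + 28 × 0.003 = 1.084.
- Noncentrality: 0.53 / (1.147 × √(2 × 1.084 / 116)) = 3.380.
- With 2 × (4 − 1) = 6 degrees of freedom the power is 0.803, against the stated 80%.
- 29 / 0.8 = 36.25, hence 37 per center, and 37 × 12 = 444.

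**Algebra.** For a child in group g, in a center of size S and in cohort C, the model as written has mean BMI at time t of

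μ + α_g + τ_t + γ_gt + β₁S + β₂C.

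With T0 as reference, so that τ₀ and γ_g0 are zero, the T1 − T0 difference is τ₁ + γ_g1. Both β terms cancel. The group difference in change is γ_g1 − γ_control,1, which does not involve S or C. If the covariates are crossed with time, the change becomes τ₁ + γ_g1 + δ₁S + δ₂C, and the contrast is then adjusted.

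**Numerical check.** Data were simulated for 12 centers × 37 children × 3 visits and fitted by REML with center and child random intercepts. Variance components, covariate effects and dropout models are assumptions.

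| Data | Effect on group-by-time estimates of adding center size and cohort as main effects |
|---|---|
| Complete, four datasets, two with true covariate effects on change | None to five decimals, SEs included (e.g. −0.44429, SE 0.11488 both ways) |
| About 20% missing at random | At most 0.0053 kg/m², about 4% of an SE of 0.12–0.13 |
| MAR dropout, about 65% seen at T2 | At most 0.0034 kg/m² |

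A separate set of 400 replicates per scenario gave a maximum shift of 0.008 with 20% missing. By contrast, in complete data the adjusted difference between the center-based arm and control in BMI **level** at T1 moved by 0.016 to 0.256.

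**What adjustment of change would do.**
- *Estimate.* Assume a cohort share of 35–65% per center and a cohort difference in 7-month change of 0.3–0.5 kg/m². Adding time interactions then moved the estimate by 0.02–0.04 on average and by up to 0.09–0.17. As a rough check on the extreme, shares of 35% in one arm and 65% in the other differ by 0.30, and 0.30 × 0.3 = 0.09 and 0.30 × 0.5 = 0.15.
- *Sampling SD.* In the same scenarios it fell by about 0.4% to 6% (0.1437 to 0.1431 at the low end, 0.1416 to 0.1337 at the high end).
- *SE with centers stratified by size.* In simulated change scores the SE stayed at 0.154 when neither covariate had an effect. It fell from 0.170 to 0.151 when size had an assumed effect of 0.1 kg/m² per SD of size. The 0.170 can be checked: ignoring size adds about 0.1² to the variance of each center mean, so the SE is about √(0.154² + 2 × 0.1² / 4) = 0.169. This applies where center-to-center variation in change enters the error term. In a model with random intercepts only, the reported SE responds less: one fitted dataset went from 0.150 to 0.146–0.147.
- *SE with size unbalanced across arms.* In the complete-data fits above, the SEs went from 0.113–0.121 to 0.115–0.172, and the contrasts moved by 0.006 to 0.140.

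**The case against.** **The text does not say main effects only.** The words about fixed effects follow a sentence on random effects and may only mark that distinction; interaction terms could be left to an analysis plan that is not shown. This is fair, but the article names one interaction and adds the covariates without any. The plain reading is main effects, and the stated contrast is left open.

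**A reader might infer that the adjustment does nothing at all.** The documents do not support that. The stated target is group differences at different time points, and for BMI level the two covariates do act. With incomplete data the cancellation is also only approximate. This does not rescue the sentence, because level is not the primary endpoint.

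**A reader might infer bias.** That does not follow either. Centers are randomized, with stratification by size, and the article groups centers so that each group has one from each condition. Leaving out the interaction causes no systematic error, only exposure to chance imbalance and possibly a larger SE.

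**Hypothesis 2.** It is tempting to carry the point over in full. But Hypothesis 2 is worded as higher or lower levels at T1 and T2, and main effects do adjust differences in level.

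**The remedy could cost precision with 12 centers.** It can when size is unbalanced across arms. With stratification by size as planned, the SE did not rise. The objection stands against crossing every optional covariate with time.

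**Conclusion.** The point holds in a limited form. As written, center size and cohort adjust BMI level but leave the T1 − T0 and T2 − T0 group contrasts essentially unadjusted: exactly so with complete data and random intercepts, and to within 0.008 kg/m² with about 20% missing. The first part follows from the model and needs no assumed effect sizes.

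The practical consequence is small for BMI. Average shifts of 0.02–0.04 kg/m² compare with a sampling SD of about 0.13–0.16 and a design difference of 0.53. They also rest on an assumed cohort difference of 0.3–0.5, which is 57% to 94% of that design difference (0.3 / 0.53 and 0.5 / 0.53). The SE benefit depends on an assumed relation of center size to change. The case for acting is that the stated adjustment should reach the stated endpoint, and that correcting it is cheap.

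**What to change.** Replace the sentence on center size and cohort with one saying that both enter **with their interaction with time**, and state that the Hypothesis 1 contrast is the group difference in change from T0, at T1 and at T2.

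Two alternatives serve equally well: model BMI change at T1 and T2 with center size and cohort as covariates, or model BMI at T1 and T2 only, with baseline BMI, center size and cohort as covariates.

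Limit the time interactions to these two pre-specified covariates. Gender, race/ethnicity and parent variables are optional in the plan, and crossing all of them with time would be too much for 12 centers.

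The cost is a few fixed-effect parameters and, for center size, one center-level degree of freedom per time contrast. No new data are needed, and the sample size calculation does not change.
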